#### Quality control

2.9

Study quality will be ensured through protocol development, standardized training, and data verification. Experts in acupuncture, gastroenterology, and statistics participated in protocol development. All personnel will receive unified training before trial initiation. During the trial, investigators will maintain appropriate communication with participants to support adherence and data integrity. Data quality checks will focus on missing values, outliers, and inconsistencies. Data entry, coding, and analysis will follow unified standards. Final data review and database locking will be conducted before unblinding.

#### Sample size

2.10

There is a lack of direct evidence on acupuncture for patients with IBS comorbid with anxiety and depression. The response rate for the SA group was derived from studies in general IBS populations because sham effects are expected to be minimal and not substantially influenced by comorbid anxiety or depression, and based on our previous study it was approximately 25% (15). For the TA group, both the established effects of acupuncture in general IBS populations and evidence from large-scale meta-analysis showing moderate-to-large effect size (Cohen’s d = 0.66) of acupuncture for depression were taken into account (13). Considering the potential secondary improvement in gastrointestinal symptoms via acupuncture targeting anxiolytic and sedative acupoints, we estimated a response rate of approximately 60% in the TA group by the end of the week 4. With α = 0.05, 36 participants per group are required to achieve 80% power. Accounting for a 10% dropout rate, a total of 80 participants will be recruited.

#### Statistical analysis

2.11

The following hypothesis will be tested simultaneously for the primary outcome:

H0: There is no difference in the response rate between the TA and SA group.

H1: There is a significant difference in the response rate between the TA and SA group.

Analyses of the treatment efficacy will be based on the modified intention-to-treat (mITT) population, which consists of all participants who were randomized and had baseline data. The safety analysis will be carried out on the safety population, which comprises individuals who received at least one dose of treatment after randomization with full recorded safety outcome. The incidence of adverse events will be determined by dividing the number of patients who experienced at least one adverse event by the total number of patients. Missing data in outcomes will be imputed five times by multiple imputation method, with the mean values been used for analysis. Continuous data will be presented as mean and standard deviation or as median and interquartile range, while categorical data will be presented in frequency and proportion. For response rate, comparison will be performed using chi - square test. For other endpoints, continuous variables will be compared using T test or the Wilcoxon rank sum test, and categorical variables will be examined using the chi - square test or Fisher’s exact test. To assess the robustness of the findings, sensitivity analyses will be conducted by truncating the data at the first use of rescue medication in repeated-measures models, and by including rescue medication and demographic characteristics use as covariates to control for its potential impact on the treatment effect estimate. Subgroup analyses will be conduct on patients with different subtypes of IBS (IBS with diarrhea, IBS with constipation, IBS with mixed bowel habits, and IBS unclassified) to evaluate the differences in the efficacy of acupuncture. All analysis will be two side and conducted using SAS 9.3 software, and a *P* value less than 0.05 will be considered statistically significant.

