### Study design

2.1

This will be a randomized controlled clinical trial involving patients with IBS. Eligible patients will be randomly allocated to the true acupuncture group (TA) or the sham acupuncture group (SA) in a 1:1 ratio. The 13-week study consists of a 1-week placebo run-in period, a 4-week treatment period and an 8-week follow-up. The study protocol was approved by the Medical Ethics Committee of Xiyuan Hospital, China Academy of Chinese Medical Sciences (Approval ID: 2025XLW019-1), and was registered (International Traditional Medicine Clinical Trial Registry: ITMCTR2025002100). The present trial will be performed following SPIRIT 2025 statement (Additional file 1). **Figure 1** shows the study flowchart. All personnel involved in this trial will receive standardized training on the trial procedures.

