#### Blinding

2.5.1

Due to the characteristics of acupuncture treatment process, only the acupuncturist and their assistant will have access to the randomization information. Patients, clinical recruiters, outcome assessors, data managers, and statisticians will be blinded to the group allocation. Unblinding of the study data will occur after the database has been locked and all participants have completed the trial.

Permitted circumstances for unblinding include (1): when a patient experiences a serious adverse event necessitating knowledge of the assigned intervention for clinical management (2); when the trial protocol contains major design flaws that threaten the scientific integrity of the results or constitute a hazard to participant rights and safety; and (3) legal requirements. If unblinding is necessary, the principal investigator will be immediately notified, and an assessment panel will evaluate the need for unblinding. If it is deemed necessary, the custodian responsible for safeguarding the randomization information will release the details according to established protocols, with the unblinding process carefully documented. The ethics committee will be informed upon completion of the unblinding.

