Safety. All adverse events occurring during the study will be monitored and recorded, regardless of their presumed relationship to the intervention. Adverse events will be classified according to severity and causality. Mild adverse events are those that do not substantially interfere with daily activities and require no specific treatment. Moderate adverse events involve noticeable discomfort or functional impairment and may require intervention. Severe adverse events are defined as life-threatening events, events resulting in significant disability, or those requiring hospitalization. For moderate adverse events, the decision to continue participation will be made in accordance with the patient’s wishes. Participants experiencing serious adverse events will be withdrawn from the trial and managed by the relevant clinical departments.

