### Data management

2.8

Paper-based materials will serve as the primary medium for data collection and storage. Clinical recruiters will be responsible for printing and archiving recruitment materials, case report forms, and informed consent documents. Acupuncturists and assistants will maintain treatment records and adverse event logs, which will be securely stored throughout the trial. To preserve blinding, research data will remain non-referential until all trial data have been collected and submitted to the principal investigator.

A standardized case report form will be established prior to enrollment, and data will be entered into EpiData software. Outcome assessors will record outcome data in the corresponding case report form sections. Any data modifications must be documented with reasons, timestamps, and signatures. Participant privacy will be strictly protected. Upon trial completion, data will undergo double entry and verification before database locking.

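### The safety population requires a complete safety record, so patients withdrawn after serious adverse events can be left out of the safety analysis, and the incidence denominator is not named

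*Protocol article*

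**What the plan says.** Section 2.11 (Statistical analysis) describes a safety population that "comprises individuals who received at least one dose of treatment after randomization with full recorded safety outcome". It has two conditions: at least one post-randomisation treatment, and a complete safety record. The article does not define what makes a record full. The same section obtains incidence by "dividing the number of patients who experienced at least one adverse event by the total number of patients", without saying which total is meant.

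The Safety paragraph of section 2.7.2 (Secondary outcomes) sets the collection rule: "All adverse events occurring during the study will be monitored and recorded, regardless of their presumed relationship to the intervention". It also says what follows an event: "Participants experiencing serious adverse events will be withdrawn from the trial and managed by the relevant clinical departments", and "For moderate adverse events, the decision to continue participation will be made in accordance with the patient’s wishes".

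On duration, section 2.1 (Study design) states: "The 13-week study consists of a 1-week placebo run-in period, a 4-week treatment period and an 8-week follow-up". The post-randomisation period is therefore 4 + 8 = 12 weeks.

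For efficacy, section 2.11 asks only for randomisation and baseline data to enter the modified intention-to-treat set, and it imputes missing outcomes.

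**The concern.** Who belongs to a safety set should not depend on anything that the treatment or its adverse events can change. Here it does. A serious event triggers withdrawal and a moderate event may lead the patient to stop, and either can cut short the record on which membership depends. The safety set is then stricter than the efficacy set: a patient withdrawn for a serious event stays in the response-rate analysis but may be missing from the adverse-event table.

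Safety is a stated aim of the trial (Introduction). With about 40 patients per arm, leaving out one patient can decide whether any serious event appears for that arm. The unnamed denominator adds a second problem, because numerator and denominator could come from different sets.

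**Working it through.** **Arm size.** Section 2.10 gives response rates of 25% and 60%, α = 0.05, 80% power, 36 per group, 10% dropout and 80 in total. Section 2.11 makes the tests two-sided. The normal-approximation formula with pooled variance under the null gives

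n = [1.96·√(2·0.425·0.575) + 0.842·√(0.25·0.75 + 0.60·0.40)]² / 0.35² ≈ 30.1, rounded up to 31.

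The continuity correction gives

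(30.1/4)·[1 + √(1 + 4/(30.1·0.35))]² ≈ 35.6, rounded up to 36.

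Then 36/0.90 = 40 per arm, or 80 in total. The plan's figures are reproduced, and the planned loss is 40 − 36 = 4 per arm.

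**Effect of the completeness condition.** Assumptions, none of them from the documents:
- all 40 patients in an arm are treated;
- the 4 planned losses are the patients without a full record;
- 6 of the 40 have at least one adverse event;
- k of the 4 lost had a serious event, these are the arm's only serious events, and the other 4 − k had no event.

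All treated patients: 6/40. Full-record patients only: (6 − k)/36. Serious events: k/40 against 0/36.

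| k | Any event, all treated | Any event, full record only | Serious, all treated | Serious, full record only |
|---|---|---|---|---|
| 0 | 6/40 = 15.0% | 6/36 = 16.7% | 0/40 = 0% | 0/36 = 0% |
| 1 | 15.0% | 5/36 = 13.9% | 1/40 = 2.5% | 0% |
| 2 | 15.0% | 4/36 = 11.1% | 2/40 = 5.0% | 0% |
| 4 | 15.0% | 2/36 = 5.6% | 4/40 = 10.0% | 0% |

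The overall rate can move either way. The serious-event rate can only be lost, because in this illustration every serious event leads to withdrawal.

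**Effect of the unnamed denominator.** If events are counted among full-record patients but divided by all 40 in the arm, k = 1, 2 and 4 give 5/40 = 12.5%, 4/40 = 10.0% and 2/40 = 5.0%. The wording does not settle which calculation applies.

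**Reading the rules together.** The collection rule in section 2.7.2 says which events are written down. The definition in section 2.11 says whose events are analysed. An event can be recorded properly and its patient still fail the completeness condition. The article has no statement that safety follow-up continues after withdrawal, or that a record complete to last contact counts as full.

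**The case against.** The best defence is that full may simply mean complete up to the patient's last contact. All events are to be recorded, so a patient withdrawn for a documented serious event could well qualify, and an analysis plan that is not shown may say so. This stands to the extent that exclusion is possible rather than certain. It does not rescue the wording: the article states the condition without that meaning, and under that meaning the condition would do little work and could be deleted.

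The defence is also right that direction is not fixed. If only event-free patients lack a full record, the rate rises to 16.7%.

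A reader might infer more than the documents support:
- **A larger bias in the true acupuncture arm.** Needling is deeper there, but no event or withdrawal rates by arm are given.
- **Run-in events being lost.** They fall within the 13-week study and so under the collection rule. All run-in patients receive sham, so these events cannot inform the between-arm comparison. A separate listing is a reporting detail.
- **Biased ascertainment by unblinded staff.** Section 2.8 says "Acupuncturists and assistants will maintain treatment records and adverse event logs", and section 2.5.1 says "only the acupuncturist and their assistant will have access to the randomization information". Section 2.8 does not make those logs the only source of safety data, and the matter is separate from how the analysis set is defined.

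Finally, the primary endpoint, its test, the sample size and the efficacy set are unaffected. That is correct and limits the reach of the point.

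**Conclusion.** The point holds as a defect in the stated definition. Membership of the safety set depends on a post-treatment condition that adverse events can affect, and the incidence denominator is not identified. As written, patients with the worst events can be left out of the safety analysis while remaining in the efficacy set.

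A reader might conclude that these patients will be removed and that the adverse-event rate is biased downward. The documents do not support that, because full is undefined and the direction depends on who leaves.

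The size is illustrative only. With 40 per arm, 4 lost and an assumed 6 patients with events, 15.0% could be reported as anything from 5.6% to 16.7%, and a serious-event rate of 2.5% to 10.0% could be reported as zero. These figures rest on the assumed event counts and on equating the planned 10% dropout with incomplete safety records.

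**What to change.** In section 2.11, delete the requirement for a full safety record. Define the safety population as all randomised patients who received at least one post-randomisation session, analysed by treatment received, regardless of completeness of follow-up. Name that set, separately for each arm, as the denominator for adverse-event incidence. Make the change before unblinding, so that it cannot appear to be driven by the data.

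The cost is a few words. Sample size, interventions, the withdrawal rules and the efficacy analysis stay as they are. The one downside is that reported event rates may change slightly.

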#### Primary outcome

2.7.1

The primary outcome will be the response rate, defined as the proportion of patients achieving a reduction of ≥50 points in the IBS-SSS (20) from baseline, which is recommended by the U.S. Food and Drug Administration (21). The primary endpoint will be the between-group comparison of response rate at week 4. The IBS-SSS consists of five items rated on a visual analog scale (0–100): severity of abdominal pain, frequency of abdominal pain, severity of abdominal distension, dissatisfaction with bowel habits, and interference with quality of life. Each item contributes equally to the total score, with an overall range of 0–500.

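### Averaging five imputed values and testing once drops the between-imputation variance and distorts the week-4 response rates; the effect is modest at the planned dropout and does not specifically favour acupuncture

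*Protocol article*

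**What the plan says.** All of the following is in the protocol article.

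- Missing data (Statistical analysis): "Missing data in outcomes will be imputed five times by multiple imputation method, with the mean values been used for analysis".
- Primary test (same section): "For response rate, comparison will be performed using chi - square test".
- Scores and the remaining continuous measures (same section) each get one test too: "continuous variables will be compared using T test or the Wilcoxon rank sum test".
- Efficacy population (same section): the modified intention-to-treat set, "which consists of all participants who were randomized and had baseline data". A patient who drops out before week 4 therefore stays in and needs an imputed outcome.
- Primary endpoint (Primary outcome): the response rate, "defined as the proportion of patients achieving a reduction of ≥50 points in the IBS-SSS", compared between groups at week 4. It is a score cut at a threshold.
- Planning rates (Sample size): about 25% response under sham; for true acupuncture, "we estimated a response rate of approximately 60% in the TA group by the end of the week 4".
- Resulting size (Sample size): the plan arrives at 36 per group for 80% power at a two-sided 5% level, and 10% dropout brings the total to 80.

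The section mentions no analysis within each imputed dataset, no combination of estimates and no between-imputation variance.

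**The concern.** Multiple imputation works by analysing each completed dataset separately and then combining the results, so that the spread between imputations enters the standard error. Averaging the imputed values first removes that spread. What remains is one completed dataset in which the filled-in values look like measurements, and which is smoother than real data.

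A thresholded endpoint adds a second problem. The average of five draws varies much less than one draw, so it falls on the majority side of the 50-point cut too often. If yes/no responses are averaged instead, the result can be a fraction such as 0.4, which cannot enter a 2x2 table without a rounding rule that the text does not give.

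At stake are the level of the only confirmatory test, the reported response rates, and the standard errors of the HADS, IBS-SSS and VAS comparisons.

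**Working it through.** **Inputs from the article.** Response 25% (sham) and 60% (true acupuncture); two-sided alpha 0.05; 80% power; 36 per group; 10% dropout; 80 in total at 1:1; five imputations; cut at 50 points.

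**Assumptions not in the article.** Normal scores; outcomes missing completely at random; regression imputation by arm; predictors explaining a share R² of 0 to 0.5 of the variance; 10% missing, with 20% as a range. The chi-square is uncorrected unless stated.

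**1. The plan's own figure.** For 25% against 60%, the uncorrected pooled formula gives 31 per group and the continuity-corrected formula gives 36. Then 36 / 0.90 = 40 per group, or 80. The stated size reproduces, but only with the correction, which matters in step 6. At 10% dropout, 0.10 × 40 = 4 patients per arm have an imputed outcome.

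**2. Standard error.** With M = 5, Rubin's total variance is T = W + (1 + 1/5)B = W + 1.2B, where W is the within- and B the between-imputation variance. A single test on averaged values has no B term and computes its variance from smoothed data. In simulation (8,000 trials per scenario, 40 per arm, R² 0 or 0.3) on the continuous score:

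| Missing | SE, averaged / Rubin | t-test error rate, averaged | Rubin |
|---|---|---|---|
| 10% | 0.90-0.92 | 6.6-8.0% | about 5% |
| 20% | 0.80-0.85 | 9.3-12.2% | about 5% |

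**3. Thresholding, closed form with no predictors.** The mean of five draws has one fifth of the residual variance, so an imputed patient is called a responder with probability Φ(√5 · Φ⁻¹(p)).

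- p = 0.25 gives 6.6%; p = 0.60 gives 71.4%.
- Whole arm at 10% missing: 0.9 × 25 + 0.1 × 6.6 = 23.2%; 0.9 × 60 + 0.1 × 71.4 = 61.1%. The difference is 38.0 points.
- At 20% missing: 21.3% and 62.3%, a difference of 41.0 points.
- If five yes/no values are averaged and rounded instead, 25% becomes 10.4% and 60% becomes 68.3% among imputed patients.

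**4. Thresholding with a fitted imputation model.** Difference in response rates in simulation, against a true 35 points:

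| Imputation model | 10% missing | 20% missing |
|---|---|---|
| No useful predictor (R² = 0) | 60.7 − 23.6 = 37.1 | 61.6 − 22.0 = 39.6 |
| Baseline correlation 0.4 | 36.8 | 38.7 |
| R² = 0.3 | 60.4 − 24.2 = 36.2 | 61.0 − 23.5 = 37.5 |
| R² = 0.5 | 36.0 | 36.6 |

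With a usable predictor the excess is about 1-2 points at 10% and 2-4 at 20%. Rubin's rules returned 25.1-25.4% and 59.8-60.0%.

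**5. Other pairs of rates.** By the formula in step 3, among imputed patients, 10% against 25% becomes 0.2% against 6.6%, so 15 points shrink to 6.4. Likewise 70% against 90% shrinks from 20 points to 11.8.

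**6. Type I error of the week-4 test.** Ranges cover null rates of 25% to 45% and the imputation models above.

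| Test | Complete data | 10% missing, averaged | 20% missing, averaged |
|---|---|---|---|
| Uncorrected chi-square | 4.5-6.0% | 6.0-8.7% | 8.2-12.3% |
| Continuity-corrected | 2.6-3.2% | 3.2-5.7% | 4.3-7.0% |

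With Rubin's rules the error was 3.9-4.9% at 10-20% missing. The excess is symmetric: at a null of 25% with 10% missing, one run rejected in 6.3% of trials, and 3.2% favoured true acupuncture.

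**7. Power as a cross-check.** At 25% against 60% with 10% missing, averaging gives 91.5-91.7%, fully observed data 90-91%, and Rubin's rules 86-88%. A method whose power rises when data are lost is overstating its information.

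**The case against.** **The wording is loose.** The phrase about mean values is ungrammatical and could mean the mean of the five estimates. On that reading the response rates are not distorted. Combination rules are also commonly left to an analysis plan, which is not shown here. What stands is that the thresholding point depends on the plain reading. The variance point does not: one chi-square test carries no between-imputation variance on either reading. Nor is this mere silence. The article states a procedure, and a plan that pooled properly would have to depart from it.

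**The effect is small at the planned dropout.** About 4 patients per arm are imputed, and IBS-SSS at baseline and week 2 is available to predict week 4. This stands. The 3- and 6-point widening in step 3 is an upper bound for a model with no predictors and should not be taken as typical.

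**The test variant is not stated.** The sample size reproduces only with a continuity correction. If the analysis also uses the corrected test, its conservatism absorbs most of the inflation at 10% missing. The uncorrected test can also exceed 5% slightly with complete data, so not all of its excess comes from imputation. Both points stand.

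**Does it favour acupuncture?** A reader might infer that both errors push towards declaring acupuncture effective. The calculations do not support that: null rejections split about evenly between the arms, and the rate distortion widens or shrinks the difference depending on where the two rates lie relative to 50%. It widens at the planning rates, but that is not a general property.

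**Conclusion.** The stated rule is wrong as written. On its plain reading it is single imputation by an average: the score standard error is about 0.90-0.92 of its proper value at 10% missing and 0.80-0.85 at 20%. At the planning rates the response difference is overstated by about 1-2 and 2-4 points respectively. Two-sided type I error of an uncorrected chi-square is about 6-9% and 8-12%, in either direction; a corrected test stays near nominal at 10%.

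These sizes rest on normal scores, data missing completely at random and an assumed imputation model, none of which the article gives. The loss of between-imputation variance does not rest on them. The problem is modest at the planned dropout and grows quickly beyond it. The documents do not support a claim of bias specifically towards acupuncture, or of certain inflation of the primary test at 10% missing.

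**What to change.** In the Statistical analysis section, delete the closing clause of the missing-data sentence and replace it with this procedure:

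1. Impute the IBS-SSS scores by arm, using baseline and the other visits.
2. Derive the response (a fall of at least 50 points) within each imputed dataset.
3. Analyse each dataset, and combine estimates and variances with Rubin's rules (PROC MI and PROC MIANALYZE in SAS).
4. Pool the continuous outcomes in the same way.

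The chi-square sentence should then refer to the pooled comparison. More than five imputations, and a sensitivity analysis counting missing patients as non-responders, are sensible but optional.

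The cost is a few lines of SAS code and a slightly wider confidence interval. Design, sample size and conduct are unchanged. The change should be made before unblinding, so that the choice cannot appear to follow the results.

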#### Secondary outcomes

2.7.2

Original IBS-SSS scores will be assessed as secondary outcomes at baseline and at weeks 2, 4, 8, and 12. The response rate will also be evaluated as a secondary outcome at baseline and at weeks 2, 8, and 12.

Hospital Anxiety and Depression Scale (HADS) (22). Symptoms of anxiety and depression will be assessed using the HADS at baseline and at week 2, 4, 8, and 12. The HADS is a validated 14-item instrument comprising two subscales for anxiety and depression. Scores are interpreted as follows: 0–7, no symptoms; 8–10, suspected symptoms; and 11–21, definite symptoms (23).

Visual Analog Scale (VAS) (24). The worst abdominal pain over the preceding 24 hours will be evaluated by VAS (0–10), with 0 indicating no pain and 10 indicating the worst imaginable pain. VAS will be evaluated at baseline and at week 2, 4, 8, and 12.

Satisfaction with bowel habits (25). Patients’ satisfaction with defecation will be assessed using a 7-point Likert scale, with response options ranging from “strongly disagree” to “strongly agree.” This scale provides an appropriate balance between sensitivity and usability, allowing for more nuanced assessment than a five-point scale while avoiding the cognitive burden of scales with more response options. Assessments will be conducted at baseline and at week 2, 4, 8, and 12.

Credibility/Expectancy Questionnaire (26). The credibility and expectancy to the intervention will be measured within 5 minutes after the first intervention session completed.

Blinding. The blinding assessment will be conducted by asking participants to guess their intervention allocation at week 2 and 4.

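### The planned arm comparisons ignore the baseline scores that the trial collects on all four efficacy scales; the tests are valid but give up precision, mainly on the continuous secondary outcomes

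*Protocol article*

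**What the plan says.** Section 2.11 names the test for each type of endpoint. For the primary: "For response rate, comparison will be performed using chi - square test". For the other endpoints, "continuous variables will be compared using T test or the Wilcoxon rank sum test", and categorical ones by chi-square or Fisher's exact test. It does not say whether the continuous tests use final scores or change from baseline.

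Covariates and repeated-measures models appear only in the sensitivity analyses of the same section. The covariates there are rescue medication and demographic characteristics; no baseline score is listed.

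The baseline values exist. Section 2.7.2 states: "Original IBS-SSS scores will be assessed as secondary outcomes at baseline and at weeks 2, 4, 8, and 12". It gives the same schedule for HADS, VAS pain and the 7-point satisfaction item. Section 2.5 places a treatment baseline assessment between the run-in and randomisation, and section 2.11 restricts the efficacy population to randomised participants with baseline data.

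**The concern.** When an outcome is measured on the same scale before and after treatment, part of its spread is explained by where each patient started. An unadjusted comparison leaves that part in the error term. With about 36 to 40 patients per arm, the loss can matter.

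It matters most for HADS. The introduction reports that the group's earlier work found no significant mental-health difference from sham and suggests mild baseline symptoms as one reason. Yet HADS will be compared here without its baseline value.

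For the primary, response is an absolute fall of 50 points from entry scores of 75 or more on a 0–500 scale. A patient starting at 75 must lose 50/75, or two thirds of the score; one starting at 400 must lose 50/400, or one eighth. Baseline may therefore predict response, though the documents do not show that it does.

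This is not a detail left to an analysis plan that is not shown: the protocol article itself names the tests.

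**Working it through.** **1. The plan's own sample size.** The inputs from section 2.10 are 25% in the sham group, 60% in the true acupuncture group ("we estimated a response rate of approximately 60% in the TA group by the end of the week 4"), and "With α = 0.05, 36 participants per group are required to achieve 80% power"; section 2.11 makes the tests two-sided.

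- Two-proportion formula with pooled variance under H0: mean rate 0.425, so n = [1.96·√(2·0.425·0.575) + 0.842·√(0.25·0.75 + 0.60·0.40)]² / 0.35² ≈ 30.1, or 31 per arm.
- With the continuity correction: (30.1/4)·[1 + √(1 + 4/(30.1·0.35))]² ≈ 35.6, or 36 per arm.
- Dropout: 72/0.90 = 80.

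Both 36 per arm and 80 in total reproduce. The exact power of the plain chi-square test with 36 per arm is 86.3%.

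**2. Continuous scales.** Let r be the correlation between baseline and week 4. The documents do not give it, so a range is assumed. With equal variances at both times and the final-score variance set to 1:

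- t test on final scores: 1
- t test on change: 2(1 − r)
- ANCOVA: 1 − r², which is (1 − r²)/[2(1 − r)] = (1 + r)/2 relative to the change-score test

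With 36 per arm, the detectable difference at 80% power without adjustment is (1.96 + 0.842)·√(2/36) = 0.66 SD. Under ANCOVA it is multiplied by √(1 − r²).

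| Assumed r | ANCOVA variance vs final score | ANCOVA variance vs change | Unadjusted final-score n per arm matching 36 with ANCOVA | Detectable difference | Power at an illustrative 0.5 SD (56% unadjusted, final score) |
|---|---|---|---|---|---|
| 0.3 | 0.91 | 0.65 | 39.6 | 0.63 SD | 60% |
| 0.5 | 0.75 | 0.75 | 48.0 | 0.57 SD | 69% |
| 0.7 | 0.51 | 0.85 | 70.6 | 0.47 SD | 84% |

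The saving is 9–49% against final scores and 15–35% against change.

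**3. Primary.** A simulation of 6,000 trials per setting, 36 per arm, compared the chi-square test with the likelihood-ratio test for arm in a logistic model that also contains baseline. The odds ratio of response per SD of baseline is an assumption.

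| Assumed odds ratio per SD | Chi-square power, 25% vs 60% | Adjusted power | Variance of risk difference, adjusted/unadjusted | Adjusted type I error, 25% vs 25% |
|---|---|---|---|---|
| 1 | 86.2% | 86.4% | 1.02 | 5.4% |
| 1.5 | 86.0% | 88.1% | 0.98 | 5.6% |
| 2 | 86.2% | 89.6% | 0.92 | 5.4% |
| 3 | 86.1% | 92.4% | 0.84 | 5.5% |

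The unadjusted likelihood-ratio test had 5.2–5.8% error in the same null runs, so the small excess over 5% belongs to that test at this sample size and not to the covariate. The chi-square test stayed at 4.6–5.1%.

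A second simulation (2,500 trials per setting) built response from the fall between correlated baseline and week-4 scores. Adjusted power was 93, 91, 90 and 89% at r = 0.4, 0.5, 0.6 and 0.7, against 86–87% for chi-square.

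**The case against.** The strongest reply is that nothing here is wrong. A chi-square test on a randomised binary endpoint is valid, matches the sample-size calculation and has more than the intended 80% power. That stands, and it limits the point to efficiency. Several stronger readings do not survive it:

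- **Chance imbalance creates false positives.** A reader might infer this. With 36 per arm, a chance baseline difference of at least 0.3 SD arises in about 20% of trials for any one scale (0.3/√(2/36) = 1.27 standard errors). But the unadjusted test's error rate already averages over such imbalances: exact chi-square size at 25% vs 25% is 4.9%. Adjustment helps interpretation when an imbalance is seen; its absence does not inflate type I error.
- **The primary is underpowered.** It is not, under the protocol's own rates.
- **Adjustment is a guaranteed gain on the primary.** Building response from a correlated baseline, as in the second simulation, itself imposes a strong link between baseline and fall: the correlation is √((1 − r)/2), or 0.55 to 0.45 for r = 0.4 to 0.6. When that correlation was set at 0 to 0.3, power changed by 0 to +2 points at 25% vs 60%, and by about −1.5 to +0.6 points at 25% vs 50%. These power figures also concern the conditional odds ratio; for the risk difference, the variance ratio is the relevant measure.
- **One headline saving applies.** A 25% saving, or 80/0.75 ≈ 107 unadjusted patients, holds only at r = 0.5. At r = 0.6 it is 36% against final scores but 1 − 1.6/2 = 20% against change.
- **Every outcome has a baseline.** The Credibility/Expectancy Questionnaire is taken once after the first session and the allocation guess at weeks 2 and 4. Neither can be adjusted in this way.

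Two further replies carry less weight. The sensitivity analyses do contain covariates and repeated-measures models, but they name no baseline score. A rank test is a defensible choice for the 7-point satisfaction item, and the fix allows for that.

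**Conclusion.** The point holds as lost precision. The protocol fixes unadjusted comparisons for four efficacy scales whose baseline values it already collects. In large samples ANCOVA is at least as efficient as a t test on either final scores or change, so the gain on the continuous secondaries does not depend on which of the two the sponsor meant. Its size does: 9–49% less variance than final scores and 15–35% less than change, for assumed r of 0.3 to 0.7.

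On the primary the gain is modest and conditional: 0 to 6–7 power points on a base of about 86%, and none if baseline does not predict response. The correlations and odds ratios are assumptions, and the variance factors are for t tests with equal variances at both visits. The change is worth making, but the planned tests remain valid without it.

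**What to change.** - **IBS-SSS, HADS, VAS pain:** replace the t and Wilcoxon tests with ANCOVA, or with a repeated-measures model over weeks 2 to 12, adjusted for the treatment-baseline score (after the run-in, before randomisation). Make the week-4 contrast the main result.
- **Satisfaction with bowel habits:** use a baseline-adjusted ordinal or rank-based analysis, or the same model as above.
- **Primary:** pre-specify, before unblinding, a response analysis adjusted for treatment-baseline IBS-SSS (for example logistic regression). Report it as a standardised risk difference with a 95% confidence interval, which stays on the scale of the protocol's hypotheses; an adjusted odds ratio is a different quantity from an unadjusted one. Show the chi-square test alongside and state which of the two is primary.

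The cost is wording and code. No new data or visits are needed, and because the efficacy population already requires baseline data, adjustment should exclude nobody.
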